## Materials and methods

### Participants

As explained above, the early onset of aggressive behavior is linked to higher biological risks and often leads to persistent antisocial behavior, highlighting the importance of applying treatment at early age. For this reason, the group to be studied will consist of 70 participants aged 10–16 years. They will be recruited from the INEBIR clinic, where the experimental sessions will be carried out, and other participants will be recruited from the Instituto Hispalense de Pediatría. The sample size was by analyzing the differences of the means according to a Student’s t with a confidence level of α=0.05, a test power of 1−β = 0.8 and a moderate effect size [30]. A moderate effect size (Cohen’s d = 0.5) represents a practically meaningful difference in the context of clinical decision-making, even if smaller effects may also be statistically detectable in larger samples and it is a commonly used convention in behavioral and clinical research when planning exploratory studies [31]. A moderate effect size results in 62 participants. For a small effect size (Cohen’s d = 0.2), we would need to recruit more than 300 participants, and we do not have the human and material resources to complete this study in a relatively short time. Additionally, to account for potential non-response or dropout, we included an additional 10%, bringing the final target sample size to 70 participants. This approach ensures sufficient power to detect differences between groups while anticipating common challenges in recruitment and retention.

To participate in this study, the following inclusion criteria will be applied:

Adolescents aged 10 to 16 whose parents seek professional help because their son or daughter exhibits aggressive outbursts that they are unable to manage.Intermittent aggressive episodes with a frequency of at least once a week in the two months prior to the start of the intervention.Not presenting some of the following:History of bipolar or psychotic disorder.Head trauma with loss of consciousness for more than 60 minutes.

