**Summary of primary variables.**

Phsycometric measures**CACIA**:**Delay of gratification percentile (RR)**: This percentile indicates the ability to postpone immediate rewards for larger, later benefits, a key aspect of impulsivity and self-control. The higher percentile the better self-control in delaying gratification.**Criterial Self-Control Percentile (CSC)** : This percentile reflects a general capacity for self-control in situations requiring judgment and adaptation to specific criteria
**CBCL and YSR****Aggressive behavior T-score**: A continuous variable reflecting the severity of aggressive behaviors reported by parents (CBCL) or the youth themselves (YSR). Scores above 60 or 65 are often considered in the clinical range.**Externalizing problems T-score**: This variable asessess a broader spectrum of outward-directed problem behaviors, including aggression, rule-breaking, and defiance. Higher scores indicate more severe externalizing problems.

Physiological measures**HR**: Measured in bpm, this continuous variable is affected by both PNS and SNS.**HRV (RMSSD)**: A continuous variable that also shows the activity of the ANS. A reduced HRV is associated to a high SNS activity in healthy subjects.**SCL**: This is a continuous variable, measured in microsiemens (μS), that reflects sympathetic activity linked to emotional arousal.

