#### Significant physiological features for aggressive outbursts detection.

We will also extend the statistical analysis to gauge how an aggressive outburst influences all physiological signals. To attain this objective, we will collect features from the last minute of relaxation period, in order to build a set to compare with the features associated with the 60-second data segment that contains the aggressive episode. For each participant there will be a maximum of 7 sets of features for any physiological signal, which will be obtained from sessions S2–S4 and S6–S9, considering that the evoking phase is successful. Statistical analysis will be applied to every feature individually. Friedmann’s test or ANOVA, with repeated measures will be applied to assess the difference between measures before and during the outburst. Friedmann’s test is a non-parametric method suitable for analyzing ordinal data or data that do not meet the assumptions of normality and homoscedasticity; it is also specifically designed for repeated measures or matched group data, allowing for comparisons across multiple conditions or time points for the same subjects. ANOVA will be applied for normally distributed data.

The analysis will be applied to each participant individually and for all participants globally. In order to reduce biases among individuals, features obtained during the baseline phase will be removed from the other phases.

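### For features judged non-normal, the two-condition before-versus-during contrast turns Friedman's test into the sign test; the power loss is modest and a paired signed-rank test avoids most of it

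*Protocol article*

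**What the plan says.** In the protocol article, the Analysis subsection on significant physiological features defines two states per evoked outburst. For the first, "we will collect features from the last minute of relaxation period"; these are gathered "to compare with the features associated with the 60-second data segment that contains the aggressive episode". Each feature is tested separately, and "Friedmann’s test or ANOVA, with repeated measures will be applied to assess the difference between measures before and during the outburst". The branch is chosen by distribution: "ANOVA will be applied for normally distributed data", with Friedman's test otherwise. The Metrics section adds that normality is assessed by Shapiro–Wilk and that the choice of test follows the residuals.

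The same subsection sets two levels of analysis: "The analysis will be applied to each participant individually and for all participants globally". On the amount of data it says "For each participant there will be a maximum of 7 sets of features for any physiological signal". The Block 2 description discards data where no outburst could be evoked, so some participants will have fewer. The features are measured on a full numerical scale. Of SCL, the summary of primary variables says: "This is a continuous variable, measured in microsiemens (μS), that reflects sympathetic activity linked to emotional arousal". HR and RMSSD are also listed there as continuous.

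**The concern.** The article supports Friedman's test by its ability to compare several conditions or time points, but this contrast has only two. Within each pair the ranks can then only be 1 and 2, so the test sees whether a feature rose or fell and not by how much. The aim is to find which features respond most to an outburst, and the Conclusion wants a small set of predictors from them. A test blind to the size of change is a weak screen for that purpose, and a feature with a real but small and skewed response could be missed. The choice of test is stated in the article, so this is not a detail left to a separate analysis plan.

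**Working it through.** **Inputs from the article.** Two conditions. At most 7 pairs per participant, which the session count reproduces: S2–S4 gives 3, S6–S9 gives 4, and 3 + 4 = 7. Sample size: "bringing the final target sample size to 70 participants". Alpha is 0.05, stated for the between-group comparison; two-sided is assumed here. The article gives no effect size or distribution for this contrast, so those below are assumptions. Effects are in SDs of the paired difference (dz) unless stated.

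**Step 1: the identity.** Friedman's statistic is Q = 12/(n·k·(k+1))·ΣR² − 3n(k+1). With k = 2 and one value per cell it reduces to Q = (2B − n)²/n, where B is the number of pairs that rise. This is the chi-square form of the sign test. Computed both ways, the two agree at n = 7 (1.286), 35 (3.457), 62 (6.452) and 70 (2.800). Rescaling the differences while keeping their signs leaves Q unchanged (0.514 both times).

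**Step 2: what it means inside the Friedman branch at 7 pairs.**
- 7 of 7 in one direction: Q = 49/7 = 7; p = 0.008 (exact 2/128 = 0.016).
- 6 of 7: Q = 25/7 = 3.571; p = 0.059 (exact 16/128 = 0.125).

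So only a unanimous result is significant. The exact signed-rank test also rejects at 6 of 7 if the one fall is the smallest change (4/128 = 0.031) or the second smallest (6/128 = 0.047).

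With chi-square p-values, 4 of 4 gives 0.0455 against a true probability of 2/16 = 0.125, and 5 of 5 gives 0.0253 against 2/32 = 0.0625.

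**Step 3: the plan's rule as a whole.** Simulated as Shapiro–Wilk at 0.05 on the paired differences, then paired t-test or Friedman. The comparator is the signed-rank test used throughout.

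| Differences | 70 pairs, dz 0.3: plan v signed-rank | 7 pairs, dz 1.0: plan v signed-rank |
|---|---|---|
| Normal | 69% v 67% | 60% v 58% |
| t5 | 72% v 78% | 65% v 64% |
| t3 | 87% v 91% | 74% v 74% |
| Laplace | 80% v 82% | 66% v 66% |
| Difference of two lognormals | 99% v 98% | 75% v 78% |

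If signed-rank replaces only the Friedman branch, the gain at 70 pairs is about 4 to 5 points for t5 and t3, and none for Laplace.

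For right-skewed (lognormal) features at 70 pairs, with signed-rank as the fallback, power rises from 65% to 76% for a shift of 0.2 log units and from 42% to 53% for 0.15, a gain of 11 points each. Across the skewed cases tried the gain is about 10 to 13 points at 70 pairs, and about 3 to 8 points at 7 pairs.

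Type I error under the two-branch rule at 4 and 5 pairs is about 4 to 6%.

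**Step 4: the unit in the global test.** The identity in step 1 needs one value per condition per block, and the article does not say how up to 7 sets per participant enter. With no average effect but effects that vary between participants, simulated type I error was about 13% with sessions as replicates within participant blocks, and about 10% with all 70 × 7 = 490 pairs treated as independent. With one mean difference per participant it was 4 to 5%.

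**The case against.** Three stronger readings are tempting, and the article supports none of them.

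- **A reader might infer that every continuous feature is reduced to up or down.** Features judged normal go to ANOVA, which with two conditions is the paired t-test and keeps the full scale.
- **A reader might infer a power loss of 20 points or more.** Friedman against signed-rank with normal differences does give 48% v 68% at 70 pairs (dz 0.3) and 29% v 56% at 7 pairs (dz 1.0). But normal differences are what the plan sends to ANOVA. At 7 pairs Shapiro–Wilk rejects in only 5 to 23% of runs, so the t-test is used most of the time.
- **A reader might infer individual error rates of 12.5% or 6.25%.** Those hold only where Friedman is used, not for the rule overall.

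It is also fair to say that the sign test needs no symmetry assumption and can match or slightly beat signed-rank when tails are very heavy. The analysis is secondary, and if sessions enter as within-block replicates the test is not a sign test at all.

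These objections cut the size of the concern, but they leave a mismatch between the stated test and a two-condition contrast, with a real loss for skewed features. The replicates reading does not rescue the plan, because step 4 shows it brings its own error-rate problem. If normality were judged on raw values instead of residuals, Friedman would be used more often and the loss could be larger, but the Metrics section points to residuals.

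**Conclusion.** The point stands in limited form. On the non-normal branch, with one value per condition per block, the named test is the sign test. The cost under the plan's own rule ranges from nothing to the low teens in percentage points of power, and is greatest for right-skewed features with small shifts in the global analysis. This rests on assumed effects and distributions, two-sided 0.05, and Shapiro–Wilk applied to the paired differences. There is no material inflation of type I error under the two-branch rule. The main comparison of change in psychometric scores between groups does not use this test. This is a cheap improvement to a secondary analysis, not a threat to the trial's main conclusion.

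**What to change.** In the subsection on significant physiological features, name the Wilcoxon signed-rank test with exact p-values as the non-parametric alternative for the before-versus-during contrast. A paired t-test on log-transformed RMSSD and SCL would also do, with logs taken before the baseline is subtracted because baseline-corrected values can be negative. In the global analysis, use one outburst-minus-relaxation value per participant. For individual analyses on the non-parametric branch with fewer than 6 pairs, report the median change without a p-value. Keep Friedman's test for three or more conditions.

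The cost is a few sentences of analysis wording and a different standard function, with no new data. There are two downsides. The signed-rank test assumes roughly symmetric differences under the null. The exact test also cannot reach 0.05 with 5 or fewer pairs (smallest two-sided p at 5 pairs: 2/32 = 0.0625), so some participants will have no individual p-value.

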#### Comparison between lab and home scenarios.

Friedman’s test will verify the statistical significance of the SCL and cardiac features between the two scenarios: home and clinic. Firstly, researchers will label the time point in which an aggressive episode takes place in the temporal series. The 60s data after those labels will be segmented using the window lengths and overlaps of 30s and 50% respectively. Features will be obtained for each window and grouped into two sets, which will be used as input to Friedman’s test or to ANOVA with repeated measures.

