The main goal of this study is to verify the efficacy of psychological treatment, in the young population, when this treatment includes biofeedback of changes in some physiological features (such as SCL, HR and HRV) associated with the imminent onset of an aggressive outburst. Apart from the main goal, other aspects will also be explored: how aggressive episodes influence physiological signals (HR, HRV, SCL in particular) identifying the most significant features; and how different scenarios (home, lab) influence this variability in physiological signals.

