S1 Families will be the active part of the experiment in the second session, which takes place at home, not at the research center. A small camera will be hidden in the living room, while the adolescents wear a wristband that records multiple biosignals (HR, SCL and skin temperature (ST)). The goal is to register the scene together with physiological variables before, during and after at least up to four aggressive outbursts.The experimenter will synchronize both the camera and the wristband, and instruct parents to extract the physiological information, make the video clip containing the aggressive episodes, and annotate when they started.

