### Materials

**Wifi camera.** A camera (model Tapo C200), which captures video and audio, will be hidden in the living room, which captures an aggressive outburst. The experimenter will synchronize this camera to the Empatica E4 wristband.

**Empatica embrace plus.** Adolescents will have to wear this wristband for several days at home. It records multiple biosignals (photoplethysmogram (PPG) [44], electrodermal activity (EDA) and skin temperature (ST)) at a sampling rate of 64Hz. Heart rate (HR) and heart rate variability (HRV) can be extracted from photoplethysmogram (PPG) and electrodermal activity (EDA) allows estimating the SCL. The camera will be synchronized to the wristband using their own internal clocks.

**Physiological recording system.** For the sake or reproducibility of the laboratory sessions, several devices, not mutually exclusive, can be used to capture subject’s biosignals. Some of them are shown below:

**AAI Wearables.** The wearable devices described in [45] capture EDA and electrocardiog-raphy (ECG) and transmit raw data through Bluetooth low energy to a laptop that converts the incoming data into LSL streams. LSL (Lab-Streaming Layer) is a C++ library that allows data synchronization from multiple sources [46].

**Emotibit.** Emotibit records the same physiological signals as Empatica E4 [47]. It is less compact but more affordable. It also allows real-time signal transmission, although its battery life is more limited. As in the case of Empatica, Emotibit will be placed at the wristband during the laboratory sessions. An application called Emotibit Oscilloscope, running on a laptop, can receive, through WiFi connection, data from the Emotibit wristband, and then redirect the physiological signals to LSL streams on the computer network.

**Psychobit** BITalino PsychoBIT [48] is a pre-assembled device designed for basic psychophysiological data acquisition. It facilitates the measurement of various physiological signals, including pulse, blood pressure, respiration, and skin conductivity. The core of PsychoBIT is BITalino (r)evolution Plugged, which offers Bluetooth communication for seamless data transmission. The kit comprises several pre-assembled sensors: ECG, EDA, PPG, etc. Data are received by OpenSignals, which is a free software that allows redirecting raw or processed information, such as HR, which is obtained from ECG or PPG, to LSL streams.

Fig 3 shows a possible schematic based on EmotiBit.

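### The exploratory home-versus-clinic comparison tests features from overlapping windows without reducing them to one value per participant per setting, and no common recording device is secured across the two settings

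*Protocol article*

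**What the plan says.** The Introduction of the protocol article lists, among aspects to be explored besides the main goal, "how different scenarios (home, lab) influence this variability in physiological signals".

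The analysis section that compares lab with home names Friedman's method and says that this "test will verify the statistical significance of the SCL and cardiac features between the two scenarios: home and clinic". The 60 s after each labelled episode are "segmented using the window lengths and overlaps of 30s and 50% respectively". The section continues: "Features will be obtained for each window and grouped into two sets, which will be used as input to" Friedman's test or repeated-measures ANOVA. It does not say what forms a block, and it mentions no averaging over windows or episodes.

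On devices, the description of S1 says that at home "the adolescents wear a wristband that records multiple biosignals". Materials identifies this as the Empatica wristband ("Adolescents will have to wear this wristband for several days at home"). For the laboratory, Materials says that "several devices, not mutually exclusive, can be used to capture" the signals. It names AAI Wearables (ECG and EDA), EmotiBit and PsychoBIT as some of the options.

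**The concern.** There are two separate problems.

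**Unit of analysis.** Windows that share half their data are not independent, and neither are windows from the same episode or the same participant. Friedman's test assumes independent blocks. Repeated-measures ANOVA has the same weakness if windows are entered as if they were independent. The number of observations is then overstated and the test rejects too often when setting has no effect.

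**Device.** If the home signals come from one device and the laboratory signals from another, any systematic difference between devices in SCL, HR or HRV looks like an effect of setting. The article does not say that the home wristband is also worn in the laboratory, that the devices are calibrated against each other, or that device enters the analysis. If the devices never overlap, no later analysis can separate device from setting.

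At stake is whether a significant result answers the question about setting. The primary comparison of therapies is not involved.

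**Working it through.** The article states no sample size, power or error rate for this comparison, so there is no figure to reproduce.

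**Inputs from the article.** 60 s segment; 30 s window; 50% overlap (15 s step); two conditions; α = 0.05 and 62 participants, or 70 with the dropout allowance (Participants); up to four home outbursts (S1).

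**Assumed inputs, not in the article.** Variance shares of 0–0.3 each for episode and for participant-by-setting; a device offset of 0.1–0.5 SD of a window value; equal numbers of paired home and laboratory episodes (1, 3 or 4).

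**Step 1: windows per episode.** (60 − 30)/15 + 1 = 3. Neighbouring windows share 15 s. If the 15 s pieces are independent, window values correlate 0.5 (neighbours) and 0 (first with third).

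**Step 2: form of the test.** With two conditions the Friedman statistic equals the sign-test statistic (2s − n)²/n, where s is the number of blocks with the home value higher. A numerical check gave 0.1333 both ways.

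**Step 3: overlap alone, windows as blocks.** Signs of two normal differences with correlation r correlate (2/π)·arcsin(r). For r = 0.5 this is 1/3. The variance of the sign count is therefore inflated by 1 + 2(1/3 + 1/3 + 0)/3 = 1.444. The actual type I error is P(|Z| > 1.96/√1.444) = P(|Z| > 1.63) ≈ 10%. Simulation (n = 62 and 70; 1, 3 or 4 episodes; 3,000 runs per case) gave 9–11%. The same analysis without overlap gave 4–6%.

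**Step 4: added clustering (assumed).**
- With the variance shares above, simulation with windows as blocks gave 13–32%.
- With 12 window pairs per participant (4 × 3) and a common correlation r of the home-minus-lab *differences*, the inflation is 1 + 11·(2/π)·arcsin(r). The table compares this with a separate simulation of 2,000 runs.

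| r | Inflation | Type I error, formula | Type I error, simulated |
|---|---|---|---|
| 0.1 | 1.70 | 13% | 13% |
| 0.3 | 3.13 | 27% | 27% |
| 0.5 | 4.67 | 36% | 38% |

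**Step 5: one mean per participant per setting.** Simulated type I error was 4–6%.

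**Step 6: device offset with no setting effect.** This uses one mean per participant per setting, n = 62, three episodes, and assumed shares of 0.3 (participant-by-setting) and 0.2 (episode).
- The mean of three overlapping windows has 5/9 of the variance of one window.
- The variance of a participant's mean in one setting is 0.3 + 0.2/3 + 0.5·(5/9)/3 = 0.459.
- The SD of the home-minus-lab difference is √(2 × 0.459) = 0.958.
- An offset of 0.2 SD gives a probability Φ(0.2/0.958) = 0.583 that the device reading higher gives the larger mean. The binomial rejection probability is then about 27%.
- Simulation gave 11%, 29%, 51% and 91% for offsets of 0.1, 0.2, 0.3 and 0.5 SD.

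Averaging therefore repairs the window problem but not the device problem.

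**The case against.** **The block is undefined, and a condensed article may leave that to a fuller document.** This is fair: windows as blocks is one reading, and the mention of repeated measures points to a within-participant structure. But the section does name per-window features as the test input. If windows were averaged first, the overlap would do no harm.

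**A reader might infer that the plan's error rate is 13–38%.** The article does not support that. A stable participant level cancels in a paired difference and leaves the error at about 5%. The higher figures need episode variance or correlated home-minus-lab differences, for which the article gives no values.

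**A reader might infer that setting and device are certainly confounded.** That is too strong. The laboratory list is open and does not exclude the Empatica. Materials says EmotiBit records the same signals and is also worn at the wrist, and Metrics says both derive HR from PPG peaks. A different sensing principle is clear only for the ECG-based options. What stands is that nothing secures a common device.

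**A reader might fault Friedman's test itself for losing power with two conditions.** A sign test is valid. Simulated power of 48% against 68% for the signed-rank test (n = 70, 0.3 SD) uses normal differences, and the plan names ANOVA as the alternative, for normal data according to the preceding analysis section. With one value per setting, that ANOVA is the paired t-test. For Laplace differences the gap is 82% against 83%.

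**A reader might point to the small number of pairs per participant**, since in the outburst-detection analysis "The analysis will be applied to each participant individually and for all participants globally". The smallest attainable exact p-value with few pairs is the same for the signed-rank test, so this is no argument against Friedman's test and no part of this point.

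**Conclusion.** The point holds in limited form. If windows are used as blocks, overlap alone roughly doubles the nominal 5% error, to about 9–11%, assuming independent 15 s pieces. Any further rise depends on assumed variances: the direction is clear but the size is unknown. Device confounding is an unsecured risk, and its size depends on an offset that the article does not give. It would not be legitimate to conclude that the comparison can say nothing about setting, or that the trial's main result is compromised. The comparison is exploratory and separate from the efficacy analysis. The point still merits action now, because same-device recordings cannot be recovered after data collection.

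**What to change.** 1. Have participants also wear the home wristband in S2–S4, and use only its signals for the home-versus-clinic comparison. If this is not done, state that setting and device cannot be separated.
2. State the unit of analysis: average windows within episode, then episodes within setting, to give one value per participant per setting. Compare these with a paired t-test or Wilcoxon signed-rank test. Alternatively, fit a linear mixed model with random effects for participant and episode.

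The cost is wearing a band the study already uses in three laboratory sessions, plus a few sentences of analysis text. The text can be settled later, but the recording step must be in place before the laboratory sessions.

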**Block 2.**

The second block consists of a recording session at the laboratory, which is repeated three times.

S2–S4 In these sessions, parents, scientists, adolescents and psychologists will meet to try and reproduce the outburst and record physiological signals before, during and after the aggressive episode.These sessions contain several phases:**Baseline register.** Initially, the researchers will set up the system and start recording a baseline reference for approximately 5 minutes [36].**Relaxation.** After the baseline register phase, adolescents will move on a relaxation phase, in which they will use an immersive Virtual reality (VR) system for 10 minutes. In this phase, participants can move into a landscape while listening to ambient sounds (birds and sea waves). VR, particularly immersive virtual reality (IVR), has demonstrated its effectiveness in therapy with people with behavioral disorders, improving emotion recognition, social skills, and attention, while diminishing their anxiety and phobias [37–39].**Evoking an outburst.** In the following phase, adolescents will watch the recorded aggressive outburst while their parents explain to the therapist the reasons that caused such an episode, including all the necessary details that favor the elicitation of a new outburst. Different videos will be used in each session to avoid the accommodation effect. Re-experiencing a situation that previously triggered an anger outburst can indeed provoke it again. This is because recalling emotionally charged events can activate the same brain areas involved in the original emotional experience [40]. According to the classical conditional model, if a particular situation has been previously associated with an anger response, re-exposure to that situation can trigger anger again due to conditioned memory [41].**Relaxation.** At the end of the episode, parents will leave the room for a while, and the participants will go to a new relaxation phase for another 10-minute period using again the VR.

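### The home-versus-lab analysis compares outburst-window levels with no reference segment, although the exploratory objective reads most naturally as a question about the response to an outburst

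*Protocol article*

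**What the plan says.** The Introduction lists two linked exploratory aims after the main goal. The first is "how aggressive episodes influence physiological signals (HR, HRV, SCL in particular) identifying the most significant features". The second is "how different scenarios (home, lab) influence this variability in physiological signals".

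The two aims have separate analysis sections.

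- **Significant physiological features for aggressive outbursts detection.** This uses the lab sessions S2–S4 and S6–S9 and is built as a contrast. For the comparison set, "we will collect features from the last minute of relaxation period", and this is set against the 60-second segment containing the outburst. To reduce differences among individuals, "features obtained during the baseline phase will be removed from the other phases".
- **Comparison between lab and home scenarios.** Only post-label data enter: "The 60s data after those labels will be segmented using the window lengths and overlaps of 30s and 50% respectively". Then "Features will be obtained for each window and grouped into two sets, which will be used as input to Friedman’s test" or to repeated-measures ANOVA. The two sets are home and clinic. No earlier segment, subtraction or change score is mentioned.

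The lab sessions (Block 2, with the same layout in S6–S9 up to the last phase) "start recording a baseline reference for approximately 5 minutes". Ten minutes of VR relaxation follow, and only then is the outburst evoked. The home session S1 (Block 1) describes neither a baseline nor a relaxation phase, but it does plan to record signals before, during and after each outburst. Under Materials: "Adolescents will have to wear this wristband for several days at home".

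**The concern.** In the second aim, the words about variability refer back to the first aim, which is the effect of an episode on the signals. That effect is a change from some prior state. The protocol treats it so in the lab analysis, where the outburst segment is set against a relaxation segment and baseline features are removed. The home/lab analysis drops the reference and compares levels during the outburst.

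The starting levels have reason to differ by design. In the lab the outburst follows a set-up baseline and ten minutes of VR relaxation. At home it arises in the living room with no preparatory phase. The home wristband may also differ from the lab recording device, although the problem would remain with a single device.

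The error can go either way. Equal responses on unequal starting levels would look like a setting effect. Unequal responses could be cancelled by an opposite difference in starting level. The Study limitations section raises the possibility that the lab environment inhibits the outburst. A level comparison cannot separate that from a lower starting point after relaxation.

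**Working it through.** The plan states no sample size, power or error rate for this comparison, so there is no figure to reproduce. The check is algebra plus an illustration on assumed inputs.

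**1. What the planned contrast estimates.** For one participant, write the outburst-window feature in a setting as starting level L plus response R. The planned home/lab difference is

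D = (L_lab + R_lab) − (L_home + R_home) = (L_lab − L_home) + (R_lab − R_home).

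The aim, read as above, concerns only the second bracket. If R_lab = R_home, D equals the level difference. If R_lab − R_home = −(L_lab − L_home), then D = 0 and a real difference in response is missed.

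**2. Data entering the test.** A 60 s segment cut into 30 s windows with 50% overlap (a 15 s step) gives (60 − 30)/15 + 1 = 3 windows per episode. All lie after the label, so none carries information on L alone.

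**3. Chance of declaring a setting effect when responses are identical.** Assumptions: one value per participant per setting; a mean level difference of δ standard deviations of the paired difference; a two-sided paired t-test at 0.05. The noncentrality is δ√n and the rejection probability comes from the noncentral t with n − 1 degrees of freedom. Both δ and n are assumed. The values of n stand for participants with usable episodes in both settings; 70 is the recruitment target.

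| n | critical t | δ = 0 | δ = 0.2 | δ = 0.3 | δ = 0.5 |
|---|---|---|---|---|---|
| 30 | 2.045 | 5% | 19% (δ√n = 1.095) | 36% (1.643) | 75% (2.739) |
| 50 | 2.010 | 5% | 28% (1.414) | 55% (2.121) | 93% (3.536) |
| 70 | 1.995 | 5% | 38% (1.673) | 70% (2.510) | 98% (4.183) |

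**4. Simulation with the tests the plan names.** Two conditions, 2,000 replicates, responses identical in both settings. Assumed SDs: person level 1.0, setting-specific resting noise 0.5, response 0.3, window noise 0.3. Shifts here are in between-person SDs. The paired-difference SD is √(2 × 0.5² + 2 × 0.3²) = 0.82, so a shift of 0.2 is δ = 0.24 on the scale of step 3.

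| n | shift | Friedman, no reference | Repeated-measures ANOVA, no reference |
|---|---|---|---|
| 30 | 0 | 4% | 6% |
| 30 | 0.2 | 19% | 27% |
| 30 | 0.5 | 72% | 90% |
| 62 | 0 | 5% | 5% |
| 62 | 0.2 | 34% | 47% |
| 62 | 0.5 | 97% | >99% |

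When each outburst value was referenced to the level in its own setting, rejection stayed at about 3.5% to 6% for every shift tried (0 to 0.8) at n = 30, 62 and 70. That simulation subtracts the starting level exactly. It therefore shows that referencing removes a pure level shift. It does not show that any particular choice of reference is unbiased.

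**The case against.** **The aim may concern levels.** The Introduction's wording is loose and never mentions change from rest. The analysis section frames its question simply as SCL and cardiac features in two scenarios. Whether outburst recordings look alike at home and in the lab is a fair question about ecological validity, and for that question a level difference is a true result. This stands in part: the 5% benchmark applies only under the response reading. That reading is still the more natural one, because the second aim refers back to the effect of episodes and the companion analysis treats that effect as a contrast.

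**Referencing may be left to a fuller plan.** The article condenses a longer protocol. However, the section does state which data segment is used and what is fed to the test, so following it as written gives the level comparison.

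**Stronger readings that the documents do not support.** A reader might infer that baseline-corrected lab values will be compared with raw home values. Nothing plans this; baseline removal is stated only under the other analysis. A reader might also infer a contrast in posture between settings, but the documents do not describe posture, and VR is used for relaxation rather than while the outburst is evoked. Nor can the percentages be taken as this trial's error rates, since they rest on assumed shifts and sample sizes.

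**References may not match.** Setting a formal lab baseline against a calm home period picked afterwards could create an artefact of its own. This stands, and it is why the fix uses one rule for both settings.

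**Conclusion.** The point holds in limited form. As written, the home/lab analysis cannot separate a difference in response from a difference in pre-outburst level, and the lab sequence makes a level difference plausible. With identical responses, the illustrative chance of declaring a setting effect runs from about 19% (0.2 SD of the paired difference, 30 participants) to 93% (0.5 SD, 50 participants). A level difference could equally mask a true difference in response. This rests on reading the aim as one about response, on one value per participant per setting, and on shifts for which the documents give no figures.

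Severity is minor. The Introduction places this among aspects to be explored apart from the main goal, and the between-arm comparison of psychological scores does not use it.

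**What to change.** In the section comparing lab and home:

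- Define the analysed feature as the outburst-window value minus the same feature from a pre-outburst window of equal length, selected by the same rule in both settings. S1 already plans to record signals before the outburst, so no new data are needed.
- Fix the interval between that window and the label in advance. Block 3 says that signals may announce an outburst at least a minute ahead, so a window touching the label could already contain part of the response.
- Compare these changes between settings within participant.
- Report the outburst-window level comparison descriptively only.
- State that lab outbursts follow VR relaxation, so the pre-outburst states are not fully equivalent even after referencing.

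The cost is a little more signal processing. Episodes without a usable pre-outburst segment drop out, and their number should be reported by setting.
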